# Observation on the effectiveness and safety of sodium bicarbonate Ringer’s solution in the early resuscitation of traumatic hemorrhagic shock: a clinical single-center prospective randomized controlled trial

**DOI:** 10.1186/s13063-022-06752-5

**Published:** 2022-09-30

**Keywords:** Traumatic hemorrhagic shock, Fluid resuscitation, Sodium bicarbonate Ringer’s solution, Lactate clearance

## Abstract

**Background:**

Traumatic hemorrhagic shock (THS) is the main cause of death in trauma patients with high mortality. Rapid control of the source of bleeding and early resuscitation are crucial to clinical treatment. Guidelines recommend isotonic crystal resuscitation when blood products are not immediately available. However, the selection of isotonic crystals has been controversial. Sodium bicarbonate Ringer solutions (BRS), containing sodium bicarbonate, electrolyte levels, and osmotic pressures closer to plasma, are ideal. Therefore, in this study, we will focus on the effects of BRS on the first 6 h of resuscitation, complications, and 7-day survival in patients with THS.

**Methods:**

/design.

This single-center, prospective, randomized controlled trial will focus on the efficacy and safety of BRS in early THS resuscitation. A total of 400 adults THS patients will be enrolled in this study. In addition to providing standard care, enrolled patients will be randomized in a 1:1 ratio to receive resuscitation with BRS (test group) or sodium lactate Ringer’s solution (control group) until successful resuscitation from THS. Lactate clearance at different time points (0.5, 1, 1.5, 3, and 6 h) and shock duration after drug administration will be compared between the two groups as primary end points. Secondary end points will compare coagulation function, temperature, acidosis, inflammatory mediator levels, recurrence of shock, complications, medication use, and 7-day mortality between the two groups. Patients will be followed up until discharge or 7 days after discharge.

**Discussion:**

At present, there are still great differences in the selection of resuscitation fluids, and there is a lack of systematic and detailed studies to compare and observe the effects of various resuscitation fluids on the effectiveness and safety of early resuscitation in THS patients. This trial will provide important clinical data for resuscitation fluid selection and exploration of safe dose of BRS in THS patients.

Trial registration.

Chinese Clinical Trial Registry (ChiCTR), ChiCTR2100045044. Registered on 4 April 2021.

**Supplementary Information:**

The online version contains supplementary material available at 10.1186/s13063-022-06752-5.

## Introduction

### Background

Severe trauma is a major global public health problem, causing an estimated more than 5.8 million deaths worldwide each year, accounting for one in ten of all deaths [1]. Blood loss due to trauma is the most important cause of death and the leading cause of death among people under 40 years of age worldwide and can cause significant economic losses. Traumatic hemorrhagic shock (THS) refers to the pathophysiological process in which trauma leads to massive loss of effective circulating blood in patients, resulting in tissue hypoperfusion, cell metabolism disorder, and organ function damage [2]. In the early stages of trauma, control of bleeding prevents death, fluid resuscitation improves tissue perfusion, and prevention of traumatic coagulopathy (TIC) reduces secondary organ failure and ultimately minimizes mortality [3–10]. Based on the above, we found that the key to clinical treatment of THS patients is rapid control of the source of bleeding, early fluid resuscitation, and restoration of intravascular volume and oxygen carrying capacity [11]. However, the choice of optimal resuscitation fluid for THS patients is still a controversial issue. Finding fluid suitable for early resuscitation is a key problem that needs to be solved urgently in clinical treatment of THS patients.

Over the past decades, many clinical studies have confirmed that early fluid resuscitation using blood products is the best option. However, blood products are often difficult to obtain immediately in the early stages of trauma. Studies have shown that pre-hospital plasma use is not associated with survival benefits in rapid ground support [12, 13]. Hypertonic crystalloids, hypotonic crystalloids, and artificial colloids have significant component differences from plasma. Their use follows many risks, such as exacerbating acidosis, causing impairment of renal function, coagulation function, platelet function, and so on [14–29]. Therefore, they are not the most optimal option. Guidelines recommend using isotonic crystalloid resuscitation in cases where blood products are not immediately obtainable [1, 25, 30]. Studies show that isotonic crystalloids with similar components to plasma become the primary option for patients with THS, except for traumatic brain injury (TBI), and fluids with the potential to restore pH may be beneficial for resuscitation [24, 25, 27, 28, 31].

Currently, the most commonly used isotonic crystalloids in clinical treatment are sodium lactate Ringer’s solution (LRS) and sodium acetate Ringer’s solution (ARS), which are distinguished by their fluid components. Lactate and acetate are metabolized in the liver and kidneys to form CO_2_ and H_2_O to maintain acid–base balance and self-clearance. THS patients lose too much blood, resulting in reduced blood perfusion to the liver and kidneys. Additional input of lactate and acetate not only increases the burden on the liver and kidneys but also aggravates the degree of acidosis due to its accumulation, accelerating the process of “bloody vicious circle” making the patient’s prognosis worse. Therefore, use of LRS and ARS is not conducive to patient resuscitation and will affect the efficacy of treatment. Sodium bicarbonate Ringer’s solution (BRS) contains the bicarbonate buffering system and its pH, electrolyte levels, and osmolality are similar to plasma. Studies show that BRS can directly participate in acid–base metabolism, modify base excess (BE) values, maintain acid–base balance, decrease lactate levels, and diminish lung cell apoptosis [32–38]. In contrast, we found that BRS, which is more similar to the plasma component, is expected to be the optimal option. Additional file 1 shows the differences between these fluid components.

At present, there are no large-scale clinical trials of early fluid resuscitation in THS patients using BRS, and systematic and detailed comparisons of the efficacy and safety of these isotonic crystals are lacking. We therefore designed this single-center, prospective, randomized controlled trial.

### Objectives

By comparing the differences in duration of shock and the lactic acid clearance rate at each time point when early fluid resuscitation was performed in the test group and control group. To identify whether early fluid resuscitation using BRS can reduce the complication rate and improve 7-day survival in patients with THS.

## Methods

### Study design

This study is a clinical single-center, prospective, superiority, parallel-group, randomized controlled trial in patients with THS. The study will be conducted at the Department of Treatment Center for Traumatic Injuries and Emergency Intensive Care Unit (EICU) of the Third Affiliated Hospital of Southern Medical University, China. Patients who meet the eligibility criteria and obtain informed consent will be assigned to the test group or control group in a 1:1 ratio based on the size of the random number allocated to them. Patients will be resuscitated with the drug according to the study arm, and only this drug will be used for resuscitation in the early fluid resuscitation (6 h) period. Approval has been obtained from the Institutional Ethics Committee (IEC) of the Chinese Ethics Committee of Registering Clinical Trials. This study complies with the Declaration of Helsinki and the relevant regulations for clinical research in China. This trial has been registered as ChiCTR2100045044.

The protocol is written in accordance with the Standard Protocol Items: Recommendations for Interventional Trials (SPIRIT) guidelines, shown in Additional file 2. Figure 1 (study scheme) shows an overview of the study process. Figure 2 shows the schedule of enrolment, interventions, and assessments.

**Fig. 1 Fig1:**
[figure not shown]
Study scheme

**Fig. 2 Fig2:**
[figure not shown]
Schedule of enrolment, interventions, and assessments. ^1^Shock Index, APACHE II, GCS score, ISS score, AIS score, NISS score, SOFA score, CRAMS score. ^2^Sodium bicarbonate Ringer’s solution group. ^3^Sodium lactate Ringer’s solution group

### Eligibility criteria

#### Inclusion criteria

Patients with THS [39, 40] (Table 1 shows the diagnostic criteria for THS)Age ≥ 18 years

**Table 1 Tab1:** The diagnostic criteria for THS. Patients who at the same time meet Clinical history, Vital signs^1^, and any three of Vital signs^2^ will be diagnosed as THS

Clinical history	Vital signs^1^	Vital signs^2^
There are traumas that cause hemorrhage (such as road traffic injuries)	(1) Systolic blood pressure (SBP) < 80 mmHg, or mean arterial pressure < 65 mmHg, or a decrease of ≥ 40 mmHg from baseline. (2) Lactate level > 2 mmol/L.	(1) Consciousness changes, includes unresponsiveness, disorientation, and confusion. (2) The skin is wet and cold with vasoconstriction and cyanosis floridis, capillary filling time > 2 s. (3) Urine output < 0.5 ml/kg/h. (4) Pulse rate > 100 beats/min or untouchable, shock index > 1.0.

### Exclusion criteria

Traumatic brain injury (TBI) and brain stem failureSevere cardiopulmonary dysfunctionSevere hepatorenal insufficiencyHypermagnesemiaHypothyroidismUsed acid correction drugsMinorities: pregnant, lactating, and prisonersTreating physician believes the patient is not suitable for the trialInability to obtain consent  Patients automatically gave up treatment or died during the study

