#### Randomization procedure

Enrolled patients will be assigned to the study arm in a 1:1 ratio based on the size of the assigned numbers via a computer-generated random number table within 10 min of admission. Before the study began, a random envelope was prepared for each bed. The envelope contains a card printed with a number (from the random number table). Once the patient is confirmed eligible to participate in the study and informed consent is obtained, the envelope will be opened and unblinding by the investigator immediately after the patient arrives at the bedside. Patient study arm is determined based on the size of the numbers on the card to ensure there is no delay in treating the patient. The investigator will not know the study arm until unblinding takes place and each envelope will be used only once.

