#### Schedule of intervention

All patients will be managed according to the standard diagnosis and treatment process, regardless of whether they participate in the trial or not. After randomization, enrolled patients will receive intervention at the set time point, as showed in Fig. 2, and they will be followed up for 7 days.

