### Outcomes

#### Primary endpoint

(A)Duration of shock(B)Lactic acid clearance rate of 6 h

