### Secondary endpoints

(A)The amount of drug use, the total amount of resuscitation fluid, and the use of vasoactive drugs was compared in each study arm.(B)The total number of deaths and mortality was compared. The Kaplan–Meier survival curve was drawn, and the 7-day mortality of patients in each study arm was compared.(C)The levels of inflammatory mediators (PLA2, TNF- α, IL-6, PCT, CRP) were compared in each study arm.(D)The recurrence rate of shock and the complications of survival cases (ARDS, AKI, TIC, MODS, etc.) were compared among the study arms.(E)Blood coagulation and platelet function (PT, APTT, TT, INR, ACT, Fib, VEM) were compared among different study arms and before and after treatment.(F)Body temperature and acidosis (T, PH, BE, Lac, PaCO_2_, HCO_3_^−^) was compared among different study arms and before and after treatment.(G)The mechanical ventilation time, EICU hospitalization time, and total hospitalization time of patients in each study arm was compared.

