#### Sample size

The trial design of this study was a positive drug, parallel-group, and superiority verification. The primary endpoint is the duration of shock and lactic acid clearance rate during the early fluid resuscitation period (6 h). Both primary endpoints were required to be met simultaneously, and Bonferroni correction was used as appropriate. The alpha value = 0.025 (one-sided), power = 0.80 were set. The total sample size was finally determined to be 400 cases with 200 cases in each study arm.

The calculations were as follows:Lactic acid clearance rate: According to a study by Wang et al., the mean value of lactic acid clearance rate after 6 h of fluid resuscitation in the control group was 32% with a standard deviation of 10%, and the expected lactic acid clearance rate after 6 h of fluid resuscitation in the test group was 35% with an equal standard deviation for both study arms [42]. The calculated sample size was 176 cases for each study arm, and a total of 392 cases were required based on 10% of the loss to follow-up.Duration of shock: According to the pre-experimental study, the duration of shock in the control group was 3 h, and in the test group the duration of shock was 1.5 h, with a standard deviation of 4 h. Assuming equal standard deviation for both study arms, the sample size calculated for both study arms was 113 cases, and a total of 252 cases were required based on 10% of the loss to follow-up.

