#### Pharmacovigilance plan

An adverse event (AE) is defined as any adverse medical event that occurs to a patient, which does not necessarily have a causal relationship with the treatment. Therefore, an adverse event can be any discomfort or unconscious signs (including abnormal laboratory results), symptoms, or disease after using the drug, whether or not it is considered drug-related. Such incidents can occur when used by the drug instructions or due to accidental or intentional overuse, drug abuse, or drug withdrawal. Any pre-existing condition or deterioration of the disease is also considered to be adverse. If it meets any of the following criteria, it will be considered a serious adverse event (SAE): the subjects died, endanger one’s life, extended hospital stay / ICU time, persistent or apparent disability/loss of function, an important medical event that requires medication or surgery to avoid serious consequences. In the event of a serious adverse event, whether or not the incident is related to the research drug or reference substance (if applicable), the doctor should notify the Research Supervision team within 24 h of the incident. The specimen management system for patients with adverse events will actively treat the patients and terminate the trial in the event of adverse events, and the remaining drugs will be uniformly recovered and centrally destroyed. The patient’s blood, body fluids, secretions, and other test-related specimens will be destroyed and recorded under the supervision of the main person in charge and the inspectorate.

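### The exclusion criteria remove patients who die or give up treatment after randomisation, which contradicts the 7-day mortality endpoint and restricts both primary endpoints to survivors who continued treatment

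*Protocol article*

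**What the plan says.** All references are to the protocol article.

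- **Exclusion criteria:** the list ends with "Patients automatically gave up treatment or died during the study".
- **Randomization procedure:** patients are allocated "via a computer-generated random number table within 10 min of admission".
- **Schedule of intervention:** after randomisation "they will be followed up for 7 days".
- **Objectives:** the trial is to find out whether BRS "can reduce the complication rate and improve 7-day survival in patients with THS".
- **Secondary endpoints, item B:** total deaths and mortality are compared, a Kaplan–Meier curve is drawn, and "the 7-day mortality of patients in each study arm was compared". The Statistical analysis section adds a log-rank test.
- **Primary endpoint:** duration of shock and 6 h lactate clearance. Under Sample size, both must be met and "The alpha value = 0.025 (one-sided), power = 0.80 were set".
- **Stopping criteria:** these include transfusion, intervention or surgery in the first hour after admission, death in the first hour after the intervention, serious adverse or unexpected events, failure to complete observation for any reason, and a request to withdraw.
- **Pharmacovigilance plan:** serious adverse events include "the subjects died, endanger one’s life, extended hospital stay / ICU time".
- **Statistical analysis:** missing data are handled by LOCF, with multiple imputation as a sensitivity analysis.

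**The concern.** An exclusion criterion should be something that can be checked before allocation. Death and giving up treatment in the course of the study come after it, and the allocated fluid can influence both. Applying the clause therefore selects patients on an outcome.

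Two things are at stake. First, the mortality comparison and the exclusion of deaths cannot both be carried out. No analysis plan can make both statements true, so this is a wrong stated rule and not a detail left to another document. Second, both primary endpoints would be compared only among patients who survived and continued. Those two groups are no longer the randomised arms. If one fluid leads to more deaths, its sickest patients drop out of the comparison, and it looks better on lactate clearance and shock duration than it is.

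The Stopping criteria could widen the problem, because the serious adverse event definition covers most poor outcomes. That list does not say, however, what happens to the data of a stopped patient.

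**Working it through.** **1. The plan's own sample size (inputs from Sample size).** For two means, n per arm ≈ 2(z₀.₉₇₅ + z₀.₈₀)²/d² = 2(1.960 + 0.842)²/d².

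- Lactate clearance: d = (35 − 32)/10 = 0.30. The normal approximation gives 175, the t-based formula 175.4, so 176. Dropout: 176/0.9 = 195.6, so 196 × 2 = 392.
- Shock duration: d = (3 − 1.5)/4 = 0.375. The normal approximation gives 112, the t-based formula 112.6, so 113. Dropout: 113/0.9 = 125.6, so 126 × 2 = 252.

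Both stated results (176 and 392; 113 and 252) reproduce. The allowance is 10%, described as loss to follow-up and not as removal of deaths.

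**2. Mortality under the clause.** The document gives no mortality rate, so take 20% v 10% as an assumption. All randomised: 200 × 0.20 = 40 deaths v 200 × 0.10 = 20 deaths, with power about 0.80 at two-sided 0.05. With deaths excluded: 160 v 180 patients analysed and 0 v 0 deaths. The zeros do not depend on the assumed rates.

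**3. Effect on the primary endpoints (simulation, assumptions throughout).** There are 200 patients per arm and no true effect. Time to resolution is lognormal with median 1.8 h and sigma 1 in both arms. Its mean is 1.8·e^0.5 ≈ 3.0 h and its SD 3.0·√(e − 1) ≈ 3.9 h, close to the plan's control values of 3 h and 4 h. The patients who die are those with the highest latent severity, which correlates with log duration at 0.3, 0.5 or 0.7. Deaths are dropped, and a rank-sum test at one-sided 0.025 is applied in favour of the arm with more deaths.

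| Mortality | Correlation 0.3 | 0.5 | 0.7 |
|---|---|---|---|
| 20% v 10%, shock duration alone | about 6% | about 11% | about 17% to 20% |
| 20% v 10%, both primary endpoints | about 1% | 1% to 2% | 6% to 8% |
| 20% v 15%, shock duration alone | about 4% | about 5% to 6% | about 7% to 8% |
| Equal mortality, shock duration alone | 2% to 3% | 2% to 3% | 2% to 3% |

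The ranges are the spread over repeated runs of 1,500 to 6,000 replicates. In the second row a null lactate endpoint is selected through the same deaths.

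**4. Room for removal.** With 200 per arm, lactate power stays at 0.80 down to 176 per arm, that is 1 − 176/200 = 12% removed. The removal rates below are assumptions.

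| Removed | n per arm | Lactate power | Duration power | Product |
|---|---|---|---|---|
| 10% | 180 | 0.81 | 0.94 | 0.77 |
| 20% | 160 | 0.76 | 0.92 | 0.70 |
| 30% | 140 | 0.71 | 0.88 | 0.62 |
| 40% | 120 | 0.64 | 0.83 | 0.53 |

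The product assumes independent endpoints. A lactate level of at most 2 mmol/L is one of the listed criteria of successful resuscitation, so the endpoints are probably positively correlated and the product probably understates joint power.

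**The case against.** The best defence is that the document as a whole points to keeping deaths. Secondary endpoint B counts them. Secondary endpoint D limits complications to surviving cases, a qualifier with no purpose if deaths were already gone. LOCF and multiple imputation presuppose that incomplete patients remain, and 10% loss is allowed for. On this view the exclusion clause is a stray line. That may well be the intention, but it supports correcting the clause: the text still tells the trial team to exclude these patients. LOCF and imputation fill in values for patients who are in the analysis; they do not bring excluded patients back.

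A reader might also infer that everyone meeting a Stopping criterion is removed from the analysis. The document does not say so. The list is headed as stopping and is silent on the data, and analysis sets are commonly left to the analysis plan. That part of the objection stands.

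A reader might further infer that both primary endpoints are certainly biased, or that the false-positive rate is 20%. Neither follows. Between-arm bias requires removal to differ by arm, and its direction depends on which arm loses more patients. The 20% figure needs a correlation of about 0.7 and concerns one endpoint, whereas the plan requires both.

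**Conclusion.** The point holds for the exclusion clause. As written, it contradicts the 7-day survival objective and the mortality, Kaplan–Meier and log-rank comparison, and it fixes observed deaths at 0 in each arm. This conclusion needs no assumption. The clause also turns both primary comparisons into comparisons among survivors who continued treatment.

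The bias that follows is a risk whose size the document cannot settle. Under the assumed 20% v 10% mortality and no true effect, false success on shock duration is about 6% to 20% for correlations of 0.3 to 0.7, and about 1% to 8% on both endpoints together. With equal mortality it stays near the nominal 2.5%. Unequal removal is plausible because the trial is open-label and stopping rests partly on the investigator's judgement.

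For the Stopping criteria the finding is conditional. If stopped patients leave the analysis, the same selection reaches further, and only 12% removal can be absorbed before lactate power falls below 0.80. The correction should be made before any data are analysed.

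**What to change.** 1. Delete death and giving up treatment from the Exclusion criteria, and reconcile the Exclusion and Stopping criteria with the Objectives and Secondary endpoints.
2. State that meeting a Stopping criterion does not by itself remove a patient from follow-up or analysis, except where consent to use the data is withdrawn. When treatment stops is a clinical question for the sponsor and is not addressed here.
3. Make the primary analysis all randomised patients in their allocated arm, with vital status to day 7 for each.
4. State how death before shock resolution, and death before the 6 h sample, enters each primary endpoint, for example ranked as the worst outcome. Without this, keeping all randomised patients does not cure the problem: such patients have no shock duration or no 6 h lactate value.
5. Keep the reduced set as a sensitivity analysis only.

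The cost is protocol and analysis-plan wording. Seven-day follow-up is already scheduled and the total stays at 400. The downside is that the estimate may be slightly diluted by patients who received little study fluid.
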